## **11.0 STATISTICAL ANALYSIS PLAN**

### **11.1 SAMPLE SIZE:**

A single retrospective cohort study in the UK demonstrated that the earlier availability of the RS results, when ordered from the post op MDT, reduced the average number of post-operative clinical appointments by 1 visit [5]. We hypothesise that the number of participant-clinician touch points in the control group is 6 visits per patient and our intervention is likely to reduce it to 5 visits per patient. With 2:1 recruitment ratio between intervention and control group and 20% dropout rate, a sample size of 330 in total is required (220 in intervention arm and 110 in control arm). This sample size was calculated by the sample size and power calculation software, nQuery [6], for comparison of numbers of touch points between intervention and standard arm using a Negative Binomial model, at 5% significance level and 90% power– see Appendix B for the screenshot of sample size calculation.

### **11.2 STATISTICAL ANALYSIS:**

The reporting guideline of CONSORT 2010 statement [7] will be followed for analysis and reporting of this study. All statistical tests and confidence intervals will be two-sided.

Ninety-five percent confidence intervals will be presented with the significance of p value at 5% significance level. Analyses will be conducted on an intention-to-treat basis (all participants who are randomized are included in the statistical analysis, including those who fail to receive an RS result from either the diagnostic core biopsy or excision specimen) and follow a pre-specified statistical analysis plan. Baseline patient characteristics will be tabulated through descriptive statistics. For the primary outcome, comparison of the numbers of participant-clinician touch points will be undertaken using a Negative Binomial model, adjusting for stratification factors and other prognostic baseline covariates. Rate of alteration in treatment pathway and rate of failure of obtaining an RS result on diagnostic core biopsy specimen in the intervention arm will be summarised and a per-protocol analysis will be conducted as secondary analysis, excluding those with alteration in treatment pathway or failure to obtain RS result. Comparison of time between diagnosis and adjuvant treatment will be assessed via Cox regression controlling for the same stratification factors and prognostic covariates. HADS score at baseline, the post-operative result clinic and commencement of adjuvant treatment will be examined by linear regression controlling for the same stratification factors and prognostic covariates. Correlation of preoperative staging with postoperative pathological staging will be calculated.

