### 3.1 INTERVENTIONS

For participants in the Standard arm, standard practice will be followed at each site for ordering and acting on the Recurrence Score® (RS®) result. The Oncotype DX® test is performed on excision samples obtained during surgery#.

#Participants receiving endocrine bridging therapy are eligible for the study provided the reason is that there has been a delay in planned surgery. Patients prescribed neo-adjuvant endocrine or chemotherapy for the purpose of downstaging are **not** permitted. In the event of the participant having received endocrine bridging therapy prior to surgery, as per routine practice, the use of the core biopsy for testing is permitted in the standard arm provided it is still ordered in the post-operative setting.

For participants in the Intervention arm, the Oncotype DX® test will be performed on the core biopsy that was taken at the time of diagnosis and the results of the Oncotype DX® test will be available to be discussed at the post-operative MDT meeting. The discussion will support decision-making on treatment options.

A failure of RS scores on the diagnostic biopsy sample would mean the test result being unavailable to support adjuvant treatment decisions for participants in the Intervention Arm. In the event of a failure on the diagnostic biopsy sample, the excision sample will be retested as per the surgical excision biopsy group. They will continue in the study in their original allocated group, being included in the primary intention to treat analysis.

Planned surgery will not be delayed if RS® results are unavailable and any change to the treatment recommendation will be recorded and discussed with the participant at an additional routine clinic appointment if required. If there is no change to the treatment recommendation, it will be left to the Centre's discretion whether to discuss the results with the patient before surgery but intentions of the centre will be recorded. If the event the decision is made to change the treatment pathway with the patient subsequently receiving neo-adjuvant or endocrine therapy prior to surgery, the clinical touchpoints, HADS and HRUQ would no longer be collected but the participants would be followed up until completion of treatment for final post-operative pathology.

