### **3.3. SECONDARY OUTCOMES**

- Time in days between the participant diagnosis (defined as the date of attendance at diagnostic clinic) and the offer and prescription of the first adjuvant cancer treatment (chemotherapy, radiotherapy or endocrine therapy)
- Time in days between the participant diagnosis (defined as the date of attendance at diagnostic clinic) and the start of the first adjuvant cancer treatment (chemotherapy, radiotherapy or endocrine therapy)

- Alteration in recommended treatment sequence. This would be defined as a when a participant in the intervention arm, as a result of the RS results from the core biopsy, receives neo-adjuvant treatment rather than proceeding directly to surgery. The clinical touchpoints, HADS and HRUQ would no longer be collected but the participants would be followed up until completion of treatment for final post-operative pathology.
- Participant reported anxiety score HADS score at the post-operative result clinic and following the offer of adjuvant treatment
- Health system cost impact analysis comparison of the intervention arm with the control arm
- Correlation of preoperative staging with postoperative pathological staging
- Rate of failure of the Oncotype DX® assay (RS result cannot be issued) on diagnostic core biopsy specimen

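### The secondary per-protocol set excludes participants for post-randomisation results of the test strategy that fall wholly or mainly on the intervention arm, so it is not a randomised comparison

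*Protocol*

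**What the plan says.** Protocol section 11.2 makes intention to treat the basis of analysis and adds that "a per-protocol analysis will be conducted as secondary analysis, excluding those with alteration in treatment pathway or failure to obtain RS result". Four other statements determine whom that rule removes.

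- **Alteration.** Section 3.3 defines it as occurring "when a participant in the intervention arm, as a result of the RS results from the core biopsy, receives neo-adjuvant treatment" instead of going straight to surgery. Sections 3.1 and 3.3 both stop collection of touchpoints, HADS and the resource-use questionnaire once it happens.
- **Failed core.** Section 3.1 says: "In the event of a failure on the diagnostic biopsy sample, the excision sample will be retested as per the surgical excision biopsy group". It adds: "They will continue in the study in their original allocated group, being included in the primary intention to treat analysis".
- **What is summarised.** The section 11.2 sentence that sets the exclusion begins by saying that the "rate of failure of obtaining an RS result on diagnostic core biopsy specimen in the intervention arm will be summarised".
- **Where an RS can fail.** The intention-to-treat sentence in section 11.2 covers all randomised participants, "including those who fail to receive an RS result from either the diagnostic core biopsy or excision specimen". Section 3.1 also says that, after endocrine bridging therapy, "the use of the core biopsy for testing is permitted in the standard arm provided it is still ordered in the post-operative setting".

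**The concern.** A per-protocol analysis normally removes people who did not follow their allocated strategy. Here both exclusion events are things that the strategy itself produces. The protocol lists alteration and core-assay failure among its secondary outcomes and prescribes what happens after each.

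Alteration depends on a core RS result being acted on before surgery. A control participant whose tumour would have given the same score cannot be identified by that event and stays in. Likewise, a control participant whose core would have failed is never tested pre-operatively and stays in. The analysis therefore compares a selected part of one arm with essentially the whole of the other. If the selection is related to the number of touchpoints, the contrast mixes the effect of the strategy with differences between patients, and it could be read as the effect when the test works.

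**Working it through.** **The plan's own figure.** The protocol gives no number for the per-protocol analysis. Its only relevant figure is the sample size (section 11.1, Appendix B): means 6 and 5, allocation ratio r = 2, dispersion 0, two-sided 5%, 90% power. With the null variance taken from the pooled rate:

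- V0 = (1+r)²/[r(6 + 5r)] = 9/32 = 0.28125
- V1 = 1/6 + 1/(2×5) = 0.26667
- n control = (1.960√V0 + 1.282√V1)² / [ln(5/6)]² = 87.07, rounded up to 88, with 176 in the intervention arm
- 88/0.8 = 110 and 176/0.8 = 220, total 330

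This matches the plan. The 88 and 176 are used below. All failure rates, alteration rates and visit differences below are assumptions.

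**Which arm each exclusion affects**

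| Event | Intervention | Control |
|---|---|---|
| Alteration (section 3.3) | Yes | Impossible by definition |
| RS failure on core | Yes | Only if the core is tested after bridging therapy |
| RS failure on excision specimen | Only on retest | Possible |

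The exclusion wording names neither arm nor specimen. It also does not say whether a failed core followed by a successful excision retest counts as a failure.

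**Failed cores with average prognosis.** Let a share f of cores fail and those participants have mean 6, while the rest of the arm has mean 5. The intention-to-treat mean is 5(1−f) + 6f.

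| f | ITT mean | ITT rate ratio | ITT difference | Per-protocol rate ratio | Complier-average difference = ITT/(1−f) |
|---|---|---|---|---|---|
| 5% | 5.05 | 0.842 | 0.95 | 0.833 | 1.0 |
| 10% | 5.10 | 0.850 | 0.90 | 0.833 | 1.0 |
| 20% | 5.20 | 0.867 | 0.80 | 0.833 | 1.0 |

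The per-protocol difference is 6 − 5 = 1.0, equal to the complier-average effect. The gap from intention to treat is a different estimand, not bias.

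**Excluded participants who differ prognostically.** Suppose there is no true effect and both arms have mean 6. A share f of the intervention arm is excluded and has d more visits than those kept. The kept mean is 6 − f·d. The error rate is for a Poisson Wald test of 88 against 176(1−f).

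| f | d | Kept mean | Rate ratio | Two-sided error |
|---|---|---|---|---|
| 5% | +2 | 5.90 | 0.983 | 6.1% |
| 10% | +2 | 5.80 | 0.967 | 9.5% |
| 20% | +2 | 5.60 | 0.933 | 23.2% |
| 10% | −1 | 6.10 | 1.017 | 6.1% |

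If these exclusions are failed cores, the complier-average estimate has the right value. The intention-to-treat difference is 0, and 0/(1−f) = 0. For f = 10% and d = +2 the exclusion set shows a false saving of 6 − 5.8 = 0.2 visits. This is the case for changing the method.

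**Altered participants.** Two calculations point in opposite directions.

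- Section 1.0 puts about 3 in 10 patients as needing chemotherapy. If 10% of the arm is removed, all from that group, its share falls to 0.20/0.90 = 22.2%. The mean falls by (0.300 − 0.222)d = 0.078d, which is 0.08, 0.16 or 0.23 visits for d = 1, 2 or 3. This needs complete counts, and chemotherapy patients having more touchpoints up to the first adjuvant offer.
- Touchpoint collection stops at alteration. If 5% are altered with 2 recorded visits against a true 6, the intention-to-treat mean is 0.95×6 + 0.05×2 = 5.8. That is a ratio of 0.967 with no true effect. Excluding them restores 6 and a ratio of 1.0, which moves the estimate against the intervention relative to intention to treat.

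**The case against.** A reader might infer that both exclusions can occur only in the intervention arm and must favour it. The documents do not support either step.

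- **Arm.** One-sidedness by definition holds for alteration only. An RS can fail on a control participant's excision specimen, or on a core tested after bridging therapy.
- **Direction.** No section says that altered participants would have had more touchpoints before the first adjuvant offer. Section 4.4 says only that staging may change the number of touchpoints. Because their counts are not collected, they lack a complete primary outcome in any analysis, and the direction depends on how truncated or missing counts are handled.
- **Failed cores.** The gap between 0.9 and 1.0 visits at 10% failure is a change of estimand, as the working shows. It is not evidence of bias.
- **Consequence.** The analysis is labelled secondary, intention to treat is primary, failed cores stay in their allocated arm there, and both event rates are to be reported. An analysis plan that is not shown may settle what counts as RS failure.

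All of this stands, and it limits the claim. It does not make the set comparable with the control arm. The exclusion rule is fixed in the protocol itself. Alteration is one-sided on the protocol's own definition, and the sentence that sets the rule speaks of core failure in the intervention arm. The truncated-count argument compares the per-protocol result with an intention-to-treat result that the collection rule has already distorted. It does not validate the exclusion.

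**Conclusion.** The point holds in limited form. The per-protocol set conditions on post-randomisation events that fall wholly (alteration) or mainly (core failure, on the natural reading) on the intervention arm. Both are results of the strategy, so the contrast is not randomised and is poorly described as per-protocol.

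Bias arises only if the excluded differ prognostically from those kept. Its sign and size are unknown. Under the assumptions shown, excluding 10% moves a null rate ratio to between 0.967 (excluded have two more visits) and 1.017 (one fewer). For altered participants the question cannot be separated from the rule that stops touchpoint collection. The primary intention-to-treat conclusion is not affected by this exclusion rule.

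**What to change.** Do not use this exclusion set as the per-protocol estimate.

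1. **Failed cores.** Report a complier-average effect with randomisation as the instrument: the intention-to-treat difference in mean touchpoints divided by the share of the intervention arm with a core RS result. The division applies to a difference in means, not to the rate ratio from the negative binomial model. It assumes that participants with failed cores follow the control-type pathway, which section 3.1 makes plausible. Label the result supplementary.
2. **Altered participants.** Do not exclude them as violators. Include them wherever outcome data exist, for example time to adjuvant treatment. For touchpoints, either continue collecting the hospital-recorded counts or treat them as missing with a sensitivity analysis.
3. **If an exclusion-based analysis is kept.** State the arm and specimen for RS failure, say whether a successful excision retest counts as failure, and label the result non-randomised.

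The cost is wording in section 11.2 and one standard supplementary analysis. The interval will be wider than the naive one. At 10% failure it is about 1/0.9 = 1.11 times the width of the intention-to-treat interval for the difference, ignoring uncertainty in the share. Continued touchpoint collection would also need changes to sections 3.1 and 3.3 and some extra site work. The missing-data route avoids that.

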## 2.0 AIMS AND OBJECTIVES

This study aims to compare the standard patient pathway (control arm), where the Oncotype DX® test is requested on the post-operative specimen with requesting the test on the pre-operative diagnostic core biopsy (intervention arm). The initial planned analyses will add to the evidence base of the patient management pathway of performing the Oncotype DX® test on the pre-operative diagnostic biopsy.

**Aim:** To assess the impact on patient management by the availability of the RS® results from the core biopsy in the pre-operative setting.

**Primary hypothesis:** The availability of the RS® results from the core biopsy in the pre-operative setting streamlines the patient management pathway

**Secondary hypothesis:** The availability of the RS® results from the core biopsy in the pre-operative setting reduces healthcare utilisation, improves patient experience and decreases the time to the offering of adjuvant cancer therapy.

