## Table of data collection

|                                                  |                                                                                                                                                                                                                                                                                                                                      |
|--------------------------------------------------|--------------------------------------------------------------------------------------------------------------------------------------------------------------------------------------------------------------------------------------------------------------------------------------------------------------------------------------|
| Baseline data                             | 
 
○ Consent
 
○ Demographics (year of birth, age, sex, ethnicity)
 
○ Histology / radiology / pathology reports on diagnostic investigations
 
○ Disease staging – TNM grading
 
○ HADS
 
○ Randomisation
 
                                         |
| Post consent                              | 
 
○ Oncotype DX® test date ordered on diagnostic biopsy (Intervention Arm only)
 
                                                                                                                                                                                                      |
| Surgery                                   | 
 
○ Results of surgery – histology, radiology, pathology reports
 
                                                                                                                                                                                                                     |
| Post-op results clinic                    | 
 
○ Oncotype DX® test date ordered (Standard Arm only) RS results delivered (intervention)
 
                                                                                                                                                                                           |

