| One week after Post-op Clinic (± 4 days)  | 
 
○ HADS and HRUQ
 
                                                                                                                                                                                                                                                                    |
| ~2 weeks after Post-op clinic             | 
 
○ RS results delivered (Standard arm only)
 
                                                                                                                                                                                                                                         |
| Adjuvant treatment offer and prescription | 
 
○ Treatment type (specifics not required as not collecting treatment outcome data)
 
○ HADS and HRUQ
 
○ Number of clinician-participant interactions and participant touch points* (Patient approach to the offer and prescription of the first adjuvant treatment)
 
 |

\* Appendix A for definitions

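### The two time-to-adjuvant-treatment outcomes are defined in days, but the only comparison named for them is a Cox hazard ratio, which does not say how many days are saved

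*Protocol*

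**What the plan says.** - **Outcomes.** Section 3.3 lists two time outcomes. The first is "Time in days between the participant diagnosis (defined as the date of attendance at diagnostic clinic) and the offer and prescription"; what is offered here is the earliest adjuvant therapy. The second runs from the same diagnostic clinic date to "the start of the first adjuvant cancer treatment (chemotherapy, radiotherapy or endocrine therapy").
- **Hypothesis.** Section 2.0 states, as part of the secondary hypothesis, that having the RS before surgery "decreases the time to the offering of adjuvant cancer therapy". No size in days is given.
- **Analysis.** Section 11.2 names one method: "Comparison of time between diagnosis and adjuvant treatment will be assessed via Cox regression controlling for the same stratification factors and prognostic covariates". It names no median, mean or restricted-mean difference for these outcomes. For HADS (section 11.2) and total cost (section 10.0) the protocol names linear regression, which does return a difference on the outcome's own scale.
- **Mechanism.** Section 1.0 says treatment would be expedited because the wait for the RS on the excision specimen disappears. The table of data collection in section 5.2 places "RS results delivered (intervention") at the post-operative results clinic, and the standard-arm result at about "2 weeks after Post-op clinic".

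**The concern.** The hypothesis is about time saved, and the Trial Summary puts time to the offer of treatment next to touch points as a measure of effectiveness. A hazard ratio can support a statement that one arm reaches treatment sooner, but it does not give the number of days.

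It is also a poor summary of the kind of effect described. If a waiting period is taken out of one pathway, the event rates in the two arms will usually differ most early on and draw together later. A single hazard ratio then averages a changing quantity, and its size depends on the variation in surgery and clinic dates as well as on the days saved. Two services with the same saving could report very different hazard ratios, and a reader could not convert either one back to days.

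**Working it through.** **What the protocol gives.** There is no effect size, SD, event count or power for the time outcomes, so there is no stated figure for them to reproduce. The only computed figure is the sample size for touch points, which supplies the numbers of participants used below. With rates 6 and 5, 2:1 allocation, dispersion 0, two-sided 5% and 90% power:

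- Pooled rate = (6 + 2×5)/3 = 5.333.
- Null variance = 1.5/5.333 = 0.28125; alternative variance = 1/6 + 1/10 = 0.26667.
- Control n = (1.960×√0.28125 + 1.2816×√0.26667)² / (ln(5/6))² = 87.07, rounded up to 88, with 176 in the intervention arm.
- Dropout: 88/0.8 = 110 and 176/0.8 = 220.

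This matches Appendix B.

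**Assumptions, because the protocol gives none.** Control mean 70 days; SD 10, 14, 21 or 28 days; gamma or log-normal times; a 14-day gain (taken from the approximate two weeks in the table of data collection) for all, half or 30% of the intervention arm.

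**Step 1: hazard ratio over time under a full 14-day shift.** If intervention times are control times minus 14, then HR(t) = h(t+14)/h(t), where h is the control hazard. At percentiles of the intervention times (gamma):

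| SD | 10th | 50th | 90th |
|---|---|---|---|
| 14 | 12.2 | 2.7 | 1.5 |
| 21 | 5.3 | 1.7 | 1.2 |

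Log-normal times show the same fall. The fall is not a mathematical necessity. With a Gompertz hazard h(t) = a·exp(bt), HR(t) = exp(14b) for every t, for example exp(0.7) = 2.0 at b = 0.05.

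**Step 2: what Cox regression reports.** 88 control and 176 intervention, no censoring, no covariates, 300 replicates per setting, gamma times, everyone gains 14 days:

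| SD | Cox HR | Mean difference (days) | Median difference (days) |
|---|---|---|---|
| 10 | 3.21 | 13.8 | 13.9 |
| 14 | 2.32 | 14.2 | 14.1 |
| 21 | 1.73 | 14.1 | 14.3 |
| 28 | 1.50 | 14.1 | 14.0 |

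**Step 3: partial benefit.** Ranges are over both distributions and all four SDs.

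| Share gaining 14 days | Mean saving (days) | Cox HR | PH test rejects | Power, Cox | Power, difference in means |
|---|---|---|---|---|---|
| 100% | about 14 | 1.50–3.21 | 74–99% | 88–100% | 97–100% |
| 50% | about 7 | 1.20–1.54 | 32–95% | 27–93% | 47–100% |
| 30% | about 4 | 1.11–1.29 | 15–65% | 10–47% | 16–88% |

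**Step 4: with dropout.** A separate simulation used all 330 participants (220/110), 20% random dropout, an assumed mean of 56 days and SDs of 10 to 28. The same 14-day gain gave hazard ratios from 3.3 down to 1.5, while the restricted mean difference stayed at 13 to 14 days. When only 30% to 50% gained, the restricted mean difference had higher power than Cox regression in every setting tried, for example 0.79 against 0.53.

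**The case against.** **Cox regression is not an error.** It is a conventional, covariate-adjusted and valid test of no difference, with 88–100% power under the full shift above. This stands, and is why it should be kept.

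**The rest belongs to the SAP.** Section 11.2 says a pre-specified analysis plan will be followed, and it is not at hand. Medians, a restricted mean or a check of proportional hazards may be in it. This stands in part: their absence from the protocol is no fault. But the protocol does not stay silent here. It fixes the comparison, and the estimate from that comparison is not in days.

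**Stronger readings that a reader might infer, and that the documents do not support:**

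- *That the timetable makes the effect a fixed two-week shift.* The table of data collection times delivery of the RS, and only approximately. It does not time the offer or start of treatment. Failed core-biopsy tests go back to the excision sample and stay in their arm (section 3.1). The first treatment may be of three types (section 3.3). Bridging therapy changes the endpoint date (section 3.2). Visits have no windows (section 5.1). A gain for only some participants is realistic.
- *That proportional hazards fails by design.* The Gompertz case shows that a shift can leave the hazard ratio constant, and with 30% gaining the test often does not reject.
- *That there is no censoring, so that ordinary linear regression of days could lead.* Section 11.1 allows for 20% dropout, and section 4.3.2 keeps data up to withdrawal. Participants who decline treatment have an offer date (section 3.2) but no start date. Linear regression needs a complete time for everyone.
- *That the trial could never state the days saved.* The dates are collected, so it could; the protocol simply does not name that comparison.

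**Conclusion.** The concern holds in a limited form. The single named comparison for two outcomes defined in days is on the hazard scale, while the hypothesis and mechanism are about removing waiting time. Under the assumed spreads, the hazard ratio for one and the same 14-day saving varies about twofold (3.3/1.5 = 2.2), while the difference in days barely moves. Non-proportional hazards are likely, not established.

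The means, SDs, distribution shapes and shares gaining are all assumptions, so the sizes are illustrative. The mismatch of scale does not depend on them. Only secondary outcomes are involved; the primary negative binomial analysis and the sample size of 330 are untouched. This is a cheap improvement, not a flaw that threatens the trial.

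**What to change.** In section 11.2, pre-specify for both time outcomes the difference between arms in restricted mean time, in days, up to a fixed horizon. Give it a 95% confidence interval, adjust for the stratification factors, use a method that handles censored participants, and make it the reported effect size. Keep the Cox regression beside it. State how participants who decline treatment are treated in the time-to-start outcome, since both methods need that rule.

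The cost is a sentence or two and one more analysis, with no new data. The horizon must be chosen in advance, without sight of results by arm, and late enough that most participants in both arms have reached the event.

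### Pre-operative against pathological staging is to be assessed by correlation, which measures association rather than agreement, and pathology after pre-surgical treatment is not separated out

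*Protocol*

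**What the plan says.** - Protocol section 3.3 lists as a secondary outcome: "Correlation of preoperative staging with postoperative pathological staging".
- Section 11.2 gives the analysis in one sentence: "Correlation of preoperative staging with postoperative pathological staging will be calculated". It names no coefficient, agreement measure, or up- or down-staging rate.
- Section 3.3 defines an altered treatment sequence, in the intervention arm, as a participant who "receives neo-adjuvant treatment rather than proceeding directly to surgery" because of the core-biopsy result. For them, touchpoints, HADS and HRUQ stop, but "the participants would be followed up until completion of treatment for final post-operative pathology". Section 3.1 repeats this rule.
- Section 11.2 sets the analysis population as intention to treat: "all participants who are randomized are included in the statistical analysis". It adds a secondary per-protocol analysis "excluding those with alteration in treatment pathway or failure to obtain RS result", without saying whether this applies to the staging outcome.
- Sections 3.1 and 4.1.2 allow endocrine bridging before surgery when surgery is delayed, without limiting it to one arm.

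**The concern.** In this trial pre-operative stage determines eligibility (sections 4.1.1 and 4.1.2), and disease staging stratifies the randomisation (section 4.4). In the intervention arm the test is done on the diagnostic core biopsy, before surgical pathology exists. The natural question for the paired stages is how often pathology gives a different stage, and in which direction. A correlation answers neither part. A fairly high coefficient could be reported while a large share of participants were mis-staged in one direction.

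The second part concerns who contributes. Pathology after neo-adjuvant or bridging treatment reflects both the original staging error and any response to treatment. If it is pooled with pathology from participants who went straight to surgery, the two cannot be told apart.

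**Working it through.** **Inputs.** The protocol gives no staging distribution, no expected mis-staging rate and no figure for this outcome, so there is nothing of its own to reproduce. All distributions below are assumptions chosen to show how the measures behave.

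**Step 1: partial up-staging.** Assume ordered categories 0 to 3, with pre-operative shares 0.50, 0.40, 0.10 and 0. A share u of each category is moved up by one at pathology and the rest agree.

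- Exact agreement = 1 − u.
- Linear weighted kappa = 1 − (observed mean category difference)/(difference expected by chance from the margins). The observed difference is u.
- Spearman = covariance of mid-ranks/√(product of their variances). Pre-operative mid-ranks, as fractions, are 0.25, 0.70 and 0.95, with variance 0.0675.

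At u = 0.3 the pathology shares are 0.35/0.43/0.19/0.03:
- Spearman = 0.0570/√(0.0675 × 0.0726) = 0.81
- kappa = 1 − 0.3/0.806 = 0.63

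At u = 0.6 the pathology shares are 0.20/0.46/0.28/0.06:
- Spearman = 0.0555/√(0.0675 × 0.0727) = 0.79
- kappa = 1 − 0.6/0.932 = 0.36

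| Up-staged | Spearman | Exact agreement | Linear kappa |
|---|---|---|---|
| 10% | 0.92 | 90% | 0.86 |
| 30% | 0.81 | 70% | 0.63 |
| 60% | 0.79 | 40% | 0.36 |
| 100% | 1.00 | 0% | 0.09 |

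From 30% to 60% mis-staging doubles and Spearman moves by 0.02. At 100% nobody has the same stage and the correlation is perfect.

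**Step 2: direction.** Transposing any of these tables turns every up-staging into a down-staging. At u = 0.3, Spearman stays at 0.81, agreement at 70% and kappa at 0.63. None of the three shows direction, so the two percentages must be reported as such.

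**Step 3: size on a continuous scale.** Assume tumour size with SD 8 mm and measurement error with SD 4 mm. The correlation stays at about 0.89 for systematic shifts of 0, 3, 5 and 8 mm. The concordance correlation, which does penalise a shift, falls from 0.89 to 0.84, 0.76 and 0.61.

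**Step 4: treated pathology.** Take 264 evaluable participants (88 + 176, Appendix B) and an assumed table with 81.4% exact agreement and 6.8% down-staged. Let a share of the 176 intervention participants switch, with pathology one or two categories lower as a result. The protocol gives no switch rate; 0 to 20% is assumed.

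| Switched | Spearman | Exact agreement | Down-staged |
|---|---|---|---|
| 0% | 0.81 | 81.4% | 6.8% |
| 5% | 0.78 | 79.8% | 8.8% |
| 10% | 0.75 | 78.3% | 10.8% |
| 20% | 0.70 | 75.3% | 14.5% |

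Agreement falls here because the assumed starting table agrees well. The effect can reverse. In the step 1 model, if treatment lowers pathology by exactly one category (and a lower category is available), up-staged participants return to agreement and agreeing ones become down-staged. Agreement among those treated then changes from 1 − u to u: from 70% to 30% at u = 0.3, but from 40% to 60% at u = 0.6. The direction depends on the unknown staging error.

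**The case against.** **The wording may be loose and the detail may sit in the SAP.** Correlation may be clinical shorthand for comparing clinical with pathological stage, and a separate analysis plan, not available here, could specify a cross-tabulation or kappa. That is possible, but the protocol uses the word both for the outcome and for its analysis. It is a stated measure rather than a gap, and it should be corrected where it stands.

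**The purpose is not stated.** The aim and hypotheses in section 2.0 do not mention staging accuracy. This stands: that agreement is the question of interest is inferred from the role that stage plays in the design.

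**Correlation is not blind to mis-staging.** This also stands. It drops from 1.00 to 0.92 at 10% up-staged and to 0.81 at 30%. The case of perfect correlation with no agreement needs every participant to move by exactly one category.

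**Eligibility restricts the range of stages.** A reader might take this as a further argument against correlation. It does not favour kappa, which also depends on the marginal distribution, so no weight is put on it here.

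**Treated pathology.** A reader might infer that the protocol feeds post-neo-adjuvant pathology into this outcome and so lowers concordance in the intervention arm only. The documents do not support that:
- No sentence says that treated pathology enters. The follow-up rule sits under the altered-sequence outcome in section 3.3 and the altered-pathway text in section 3.1.
- The per-protocol analysis excludes altered pathways and might be applied here.
- Bridging is not limited to one arm, and the outcome is not stated as a comparison of arms.
- Step 4 shows that the direction is open.

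What remains is that the all-randomised population, the follow-up to pathology and the lack of any exclusion for this outcome leave the mixing possible.

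**Conclusion.** The point holds for the choice of measure. Sections 3.3 and 11.2 specify a correlation for paired stages; it cannot show direction and responds poorly to a systematic shift. The size depends on assumed tables: with 50/40/10% pre-operative categories, a doubling of up-staging from 30% to 60% costs 30 percentage points of agreement and 0.02 of Spearman. These are not expected values for this trial. Insensitivity to a uniform shift, however, is a property of the measure and does not depend on them.

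On treated pathology the conclusion is narrower: its inclusion is possible and not ruled out, its amount is unknown and its direction is undetermined.

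The importance is low. The outcome is secondary and descriptive and has no bearing on the primary analysis or the sample size.

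**What to change.** In sections 3.3 and 11.2, replace or supplement the correlation with:

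- a cross-tabulation of pre-operative against pathological stage, T and N separately;
- exact agreement, percentage up-staged and percentage down-staged, each with a 95% CI;
- weighted kappa as a summary only, since it does not show direction either.

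State that the main staging analysis uses participants who had surgery without prior systemic treatment. Report those who had neo-adjuvant or bridging endocrine treatment before surgery separately.

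The cost is about one sentence in each section. The data collection table in section 5.2 already includes baseline TNM and surgical pathology, so no new data are needed. The drawback is a slightly smaller main set for this outcome.
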